**Fig. 1 Fig1:**
[figure not shown]
Stepped-wedge study design. C, control; I-P, FHM intervention only for patients; I-D, FHM intervention only for doctors; I-B, POFHM intervention both for doctors and patients

#### Blinding

Given the features of SW-CRT, blinding doctors and researchers is impossible. Patients will be re-recruited at each phase, and they are blind to the allocation scheme. Analyses will be performed by a researcher blinded to the PHCs allocation scheme.

### Study procedures

During the preparation phase, standard operating procedures (SOPs) for each phase have been developed according to characteristics of PHCs, including investigation process and norms, questionnaire survey instructions and training manuals. A pre-survey will then verify the validity and accuracy of the questionnaire and the survey plan. In addition, we will recruit local people experienced in the investigation as volunteers and then conduct unified training for SOPs. During the implementation phase, volunteers will deliver the intervention to patients. At the same time, the research assistant will do it to doctors, and the research assistant will be on-site throughout to ensure the intervention implementation process is standardized and uniform.

### Data collection procedures

All patients will be informed of the study information orally and in writing before the investigation or intervention. Their data will be collected only after providing written informed consent. All information about patients and doctors will be collected by questionnaire. The data collection norm is described in the SOPs. Paper questionnaires will be double entered through EpiData 3.1 version to ensure the accuracy of the information. Electronic questionnaires will be exported through the online "Questionnaire Star" platform (https://www.wjx.cn).

To better understand any potential factors that may explain the trial results, a qualitative evaluation based on TDF will be conducted after the trial is completed to assess family doctors' and patients' perceptions and experiences about the trial.

### Statistical analysis

We will use cluster-specific methods because randomization will be performed at the PHC level. For all primary outcomes, an intention-to-treat analysis will be performed. To evaluate the effects of the primary outcomes of the three interventions, generalized linear mixed models will be used, specifying the PHC effect as random and the time effect as fixed [59, 60]. Multiple imputations using chained equations will be used in case of missing data. Subgroup analyses will be conducted to evaluate the interventions' effect in different regions. All analyses will be carried out using Stata 17.0 software. A 2-tailed error rate of 5% will be used to test the hypothesis.

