In all, this study aims to evaluate the effectiveness of the POFHM intervention in primary health care institutions. POFHM is a promising intervention that integrates the four-habit theory, mindfulness theory, and patient-centered concept, providing education on four habits for mainly patients and then doctors during medical visits. The program ultimately expected to enhance the doctor-patient relationship in China, based on primary healthcare institutions. Initially, this study will evaluate the effectiveness of POFHM intervention, followed by conducting a manipulation check and process evaluation, in accordance with the implementation science framework [35]. Therefore, the results of POFHM can serve as a valuable reference for regions with limited medical resources and collectivist cultures.

In order to achieve full coverage of beneficial interventions and assess the impact of interventions, we will employ a stepped wedge cluster randomized trial (SW-CRT) [36]. The stepped wedge design enables the effectiveness of intervention programs to be tested systematically in a controlled manner. Firstly, clusters in a stepped wedge design effectively transition from the control group to the intervention group. At each phase, outcomes are evaluated among study participants in all clusters, ensuring that each cluster contributes data in both the control and intervention conditions [36]. Secondly, the stepped wedge design is advantageous as it permits researchers to progressively introduce and assess the various components of an intervention, while continuously optimizing the intervention [36]. Examples of stepped wedge investigations include the efficacy of 3 cancer pain guideline implementation strategies [37] and effects of a preschool-based sleep health literacy program [38]. The POFHM intervention is brief, and patients are unlikely to have repeat medical visit in the short term. Therefore, this study uses a cross-sectional and incomplete SW-CRT [39, 40], with a specific study design presented below.

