## Methods

### Participants

#### Study sites

There were two primary reasons for selecting the implementation site. Firstly, we acknowledged that the economic level and the distinction between urban and rural areas may impact the efficacy of POFHM intervention. Secondly, we aim to verify that the intervention is effective for the majority of Chinese. To ensure that our sample is both representative and universal, we plan to recruit four PHCs in each of our chosen regions, Nanling County and West Lake District in China, which display significant differences. Please refer to Table 1 for an overview of the key components of the stepped wedge design.

**Table 1 Tab1:** Key characteristics of the POFHM trial

Trial characteristics	Definition
Cluster (unit of randomization)	Hospitals or Primary health care facilities (a total of 8)
Number of sequences (steps)	4 (2 hospitals per sequence)
Duration of trial	1 month
Number of measurement periods	7 (length of each period is 3 days)
Individuals	Patients (greater than or equal to 16 years old) visit a doctor at any time during the study
Timing of start of exposure	Patients are exposed to the process when they wait to be seen
Duration of exposure	Patients are exposed for a short period during their visit to the doctor
Measurement	Repeated measurements are from mostly different patients in each period; a tiny proportion of individuals may have repeat visits to the same hospital

The scope of the patient concept in this study extends beyond just the patients themselves and includes their family members and friends

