### Sample size

According to our previous work, an absolute increase of 0.13 or more in DPC scores for patients is meaningful. Our sample size of eight clusters (1272 patients) achieves 80% power to detect a 0.13 absolute difference using a two-sided test at the 5% significance level [55, 56]. Our calculation assumes an intra-cluster correlation coefficient of 0.034 [57], an average of 53 patient encounters per site in each 3-day interval. While our study is a cluster RCT, given the cross-sectional nature of a stepped-wedge design and brief intervention period, the effect of individual autocorrelation coefficients (IAC) and cluster autocorrelation coefficients (CAC) on power is negligible, therefore we did not adjust for IAC and CAC [39, 58]. In conclusion, we aim to include 1590 patients to account for a degree of missing data.

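### With only 8 PHCs and no small-sample inference named, the planned mixed model would not reliably hold its 5% level under ordinary Wald z tests (about 5-15% by ML, 5-9% by REML)

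*Protocol article*

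**What the plan says.** Three places in the protocol article bear on this.

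- **Statistical analysis.** For the three interventions, "generalized linear mixed models will be used, specifying the PHC effect as random and the time effect as fixed". The section adds that "All analyses will be carried out using Stata 17.0 software" and that "A 2-tailed error rate of 5% will be used to test the hypothesis". Missing data are to be handled by chained-equation multiple imputation. ML, REML, z, t, Kenward-Roger, Satterthwaite and permutation are not mentioned.
- **Study sites, Table 1, and Background.** There are 8 units of randomisation in 4 sequences of 2, with 7 measurement periods of 3 days. The Background states that "this study uses a cross-sectional and incomplete SW-CRT".
- **Sample size.** "Our sample size of eight clusters (1272 patients) achieves 80% power to detect a 0.13 absolute difference", two-sided at 5%, with an ICC of 0.034 and an average of 53 encounters per site per 3-day interval. The section explains why autocorrelation was left out of the calculation but does not discuss the number of clusters.

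**The concern.** A Wald z test treats the standard error as known. Here the between-PHC variance is estimated from 8 PHCs, and the fixed part of the model (6 or 7 period effects plus 3 intervention effects) is estimated from few PHC-period cells. Each PHC moves in the same order, from control to a single-target intervention to both, so intervention is partly aligned with calendar time. Once time is adjusted for, the effects lean on comparisons between PHCs. ML then tends to understate the PHC variance, and the z reference ignores the uncertainty in that estimate. This happens even when the random-intercept model is exactly right, so it is a separate matter from the autocorrelation assumption.

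At stake are the p-values and intervals for every intervention contrast. A false claim of benefit would be more likely than the stated 5%, and a power figure based on a normal reference would be too high for a test that does hold its level.

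**Working it through.** **Inputs.** Sample size section: 1272 patients, 53 per PHC-period, ICC 0.034, 80% power, difference 0.13. Table 1: 8 PHCs, 4 sequences, 7 periods. Statistical analysis: random PHC effect, fixed time, three interventions, two-tailed 5%. Assumed: normal outcome, equal cell sizes, cluster autocorrelation of 1, and the placement of cells over calendar time (Fig. 1 is not shown).

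**Cells.** 1272 / 53 = 24 PHC-periods, and 24 / 8 = 3 measured periods per PHC.

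**The plan's own power figure.** It cannot be reproduced, because no SD or target contrast is given. For one pooled effect in a 24-cell staircase the standard error is about 0.095 x SD. With SD 0.488, power = Φ(0.13/(0.095 x 0.488) - 1.96) = Φ(0.84) = 80%. With SD 0.50 it is 78%. For three separate effects, 80% would need an SD of about 0.22-0.42, depending on layout and contrast.

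**Residual degrees of freedom by simple counting.** Cells - fixed parameters - (PHCs - 1):

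- 6 periods, 3 effects: 24 - 9 - 7 = 8
- 7 periods, 3 effects: 24 - 10 - 7 = 7

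As a rough guide, using 1.96 when the true reference is t gives a two-sided error of 8.6% at 8 df and 9.1% at 7 df.

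**Simulation under no true effect.** 8,000 data sets per layout; type I error in %, in the order patient-only, doctor-only, both. Offsets are the measured periods counted from each sequence's start. Mixed means the two PHCs of a sequence receive different single-target interventions; same means they receive the same one.

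| Offsets, single-target allocation | Periods | ML, z | REML, z | REML, t on counted df |
|---|---|---|---|---|
| 0,1,2 mixed | 6 | 6.8, 6.8, 10.6 | 5.4, 5.6, 7.7 | 2.7, 2.6, 4.4 |
| 0,1,2 same | 6 | 12.2, 14.8, 12.4 | 7.7, 9.1, 7.4 | 4.2, 5.3, 4.1 |
| 0,1,3 mixed | 7 | 7.4, 7.9, 13.5 | 5.7, 6.2, 8.9 | 2.4, 2.6, 4.8 |
| 0,1,3 same | 7 | 10.0, 8.6, 13.8 | 6.9, 6.2, 8.5 | 2.9, 2.5, 4.6 |
| 0,2,3 mixed | 7 | 10.4, 10.7, 12.9 | 7.3, 7.4, 8.6 | 3.3, 3.4, 4.9 |
| 0,2,3 same | 7 | 10.9, 10.9, 13.9 | 7.2, 6.9, 8.6 | 3.4, 3.4, 4.5 |

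The simulation standard error near 5% is √(0.05 x 0.95 / 8000) = 0.24 points, so the smallest REML-z excess (5.4%) is barely distinguishable from 5%. Further runs with other assumed 24-cell layouts widen the ranges to about 5-15% for ML with z (about 7-14% for the combined intervention) and about 5-9% for REML with z.

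**Does the remedy work?** REML with Kenward-Roger degrees of freedom gave 4.6-6.1% over eight layouts (4,000 data sets each). The median df for the combined intervention was about 7-12 in most layouts and 26 in one. The counted-df t test in the table is safe but often conservative.

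**Interval width.** At 8 df the critical value is 2.31 against 1.96, which makes intervals about 18% wider. At 6 df it is 2.45, about 25% wider.

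**Power, for illustration only.** A contrast with 80% power by z has non-centrality 1.96 + 0.84 = 2.80. Against a non-central t its power is 67% at 7 df, 69% at 8, 71% at 10 and 73% at 12.

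**Mildest case.** Measuring all 8 x 7 = 56 cells would give only 5.2-6.0%, but 56 x 53 = 2968 patients, which does not match 1272.

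**The case against.** The strongest reply is that the article is silent rather than wrong. It names a model class, software and a test level, but not ML, not z, and not uncorrected inference. Estimator and degrees of freedom are often settled in an analysis plan, which is not shown, and the remedy fits inside the planned model class and the named software. This stands in part. A reader might infer that the trial will reject a true null 6-15% of the time, or up to three times as often as stated. The documents do not support that as a fact: it assumes ML with z, and the top of the range combines the least favourable layout, contrast and estimator.

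A reader might also infer that the 80% power is wrong. That cannot be shown either, because neither the method nor the SD behind it is given. Nor can the size be carried over to sense of control and patient literacy as a result, since the ICC of 0.034 appears only in the communication-score calculation.

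Two practical objections also stand. Permuting whole timelines tests only the joint null that no intervention has any effect, not each intervention separately. And the planned multiple imputation means that the degrees of freedom must also be handled when results are pooled.

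What does not stand is that this is mere detail. The article commits to a 5% error rate with 8 randomised units, and ordinary Wald inference from the model it states does not reliably deliver that rate.

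**Conclusion.** The point holds in conditional form. With 8 PHCs and 24 PHC-period cells, ordinary z inference from the stated model gives a type I error of about 5-15% under ML (about 7-14% for the combined intervention) and about 5-9% under REML, with intervals too narrow to match. These ranges rest on an ICC of 0.034, 53 patients per cell, a correctly specified random-intercept model and assumed layouts. Confidence is high in the direction and moderate in the size: under REML in favourable layouts the excess is small. For the two primary outcomes without a stated ICC, the same size is an assumption. The effect on power is an illustration that applies only if the 80% came from a normal reference.

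**What to change.** - **Statistical analysis section.** State that each primary score is analysed with a linear mixed model fitted by REML, with Kenward-Roger (or Satterthwaite) degrees of freedom and t-based p-values and intervals. In Stata this is of the form `mixed ..., reml dfmethod(kroger)`. State that small-sample degrees of freedom are also used when pooling over imputations, and how they are obtained.
- **Optional sensitivity analysis.** Permute timelines among PHCs within region, described as a test of the joint null of no effect of any intervention. If each region has one PHC per sequence, there are 4! x 4! = 576 allocations.
- **Sample size section.** State whether the 80% rests on a normal reference and, if so, restate it with a t reference, giving the SD and the target contrast.

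The choice should be fixed before the data are analysed. The cost is a few sentences, some care at the imputation step, somewhat wider intervals and possibly a lower stated power. No extra patients, sites or data are needed.

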#### Intervention development and description

The interventions adopted in the study are effective in tertiary care hospitals. Implementing scientific assessments identified obstacles and promoting factors, integrating the intervention with routine procedures reduces implementation difficulty, although doctors still experienced an increase in workload, as detailed in the pilot study [41] On this basis, the interventions were adapted and piloted to the characteristics of primary healthcare facilities. First, we conducted semi-structured interviews with doctors in PHCs, revealing that primary care facilities' patient population is predominantly elderly with chronic illnesses and children with common illnesses. Doctors believed that whether patients trust them has the most significant impact on DPC. The lack of patients' health literacy would impair the effect of treatment and undermine doctor-patient trust. Therefore, we adapted the interventions based on these findings to promote DPC in primary care settings.

We then identified feasible implementation methods. Considering physicians' workload and primary healthcare facilities' primary patients, we determined to recruit volunteers to deliver the intervention to patients. During the waiting period, volunteers will engage with patients in the waiting area, provide pre-visit education on the POFHM, and administer a questionnaire after their visit.

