#### Intervention 1: FHM only for patients

The POFHM intervention program for patients consisted of four good habits during visits (see Table 2). The intervention plan was not implemented by making booklets (although we did this in the previous plan) but by recruiting volunteers to ask patients questions to implement the intervention. On the one hand, the potential subjects' visual impairment and limited educational level were considered. On the other hand, hearing a question that requires an answer can better promote patients' thinking, which is the critical point of the intervention design. Below are the detailed implementation points for the four habits.

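### The stated primary model has no patient-level term, although each PHC-period is a new patient sample recruited after the PHC's condition is set; adjusting for a few pre-visit characteristics would be a cheap improvement

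*Protocol article*

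**What the plan says.** The Statistical analysis section gives the primary model for the three interventions as a generalized linear mixed model, "specifying the PHC effect as random and the time effect as fixed". It mentions intention to treat, multiple imputation and subgroup analyses by region. It names no patient-level covariate and no adjusted analysis.

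On who enters each cell, Table 1 says "Repeated measurements are from mostly different patients in each period", and the Blinding section says "Patients will be re-recruited at each phase, and they are blind to the allocation scheme". The Recruitment section has patients enrolled on arrival, and the Randomization section has each PHC already assigned to a timeline.

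On staff, the Blinding section says that "blinding doctors and researchers is impossible". The section on intervention development says that volunteers will "provide pre-visit education on the POFHM, and administer a questionnaire after their visit".

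On case mix, the same section reports that the PHCs' "patient population is predominantly elderly with chronic illnesses and children with common illnesses". The section on Intervention 1 explains the oral format by noting that potential subjects' "visual impairment and limited educational level were considered". Data collection procedures adds: "All information about patients and doctors will be collected by questionnaire".

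**The concern.** Randomizing PHCs to timelines balances PHCs in expectation. It does not by itself balance patients who are enrolled afterwards, period by period. The random PHC effect handles a PHC's average mix of patients, and the fixed time effect handles a change in mix that all PHCs share in a period. Neither handles a change within one PHC between its control and its intervention periods.

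The document describes a population mixed in age, illness and education, and its concept of patient extends to family and friends. These features plausibly relate to patient literacy, sense of control and ratings of the doctor.

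There is also a plausible route to a shift without any intent. In control and doctor-only periods the volunteers keep order and survey after the visit. In the other intervention periods patients are also asked several sets of questions and given a task before the visit, so taking part costs more. If fewer elderly or less educated people agree under that burden, the intervention cells differ in who answers as well as in what they received.

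**Working it through.** **1. The plan's own figures.** With 53 patients per PHC and period, 1272 / 53 = 24 cells, or 24 / 8 = 3 measured periods per PHC. The inflated target is 1272 / 0.80 = 1590, an implied 20% allowance. Both reproduce. The 80% power for a difference of 0.13 cannot be checked, because no outcome SD is given and the design figure is not shown. With ICC 0.034, 53 per cell, random PHC and fixed time, one common intervention effect needs an SD of about 0.49 to 0.51 in two assumed layouts and 0.33 in a third.

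**2. Chance differences.** For a characteristic with 50% prevalence, the difference in share between two cells of 53 has SD √(2 × 0.25 / 53) = 0.097. A move of 10 points between two single cells is therefore ordinary. It is part of the patient-level residual variance, and so of the standard error. In 4000 simulated null trials per scenario with such a covariate left out (effect 0.3 or 0.5 SD, two assumed layouts), mean bias was about 0 and type I error 4.5 to 5.2%.

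**3. Selective shift.** Let the covariate effect be b (in outcome SD) and let its prevalence be higher by δ in all intervention cells. The omitted term then adds b × δ to the intervention coefficient. The document gives neither b nor δ; both are assumed here.
- δ = 0.10: bias is 0.10 × 0.3 = 0.03 SD to 0.10 × 0.5 = 0.05 SD.
- Type I error is Φ(−1.96 + bias/SE) + Φ(−1.96 − bias/SE). For one common effect the SE is 0.095 or 0.091 SD in the first two layouts. Bias/SE is then 0.32 to 0.33 at the lower bias and 0.53 to 0.55 at the higher, giving about 6.2 to 6.3% and 8.2 to 8.5%. Simulation gave 6.3 to 8.6%.
- In the third layout the SE is 0.140 SD, and the same formula gives 5.5 to 6.5%.
- For three separate effects the SEs are larger, 0.128 to 0.214 SD. The bias is unchanged, but type I error is only about 5 to 7% (0.03 / 0.214 = 0.14 gives 5.2%; 0.05 / 0.128 = 0.39 gives 6.8%).

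On the outcome scale, if the SD were 0.5, the bias would be 0.015 to 0.025 points, or 0.015 / 0.13 = 12% to 0.025 / 0.13 = 19% of the target difference. That SD is also an assumption.

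**4. Precision.** Suppose the covariates explain a share R² of patient-level variance and PHC variance is unchanged. Generalized least squares on the 24 cells, with three separate effects and the same three layouts, gives these SE ratios:

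| R² | SE ratio | Reduction |
|---|---|---|
| 0.05 | 0.982–0.994 | about 1–2% |
| 0.10 | 0.964–0.987 | about 1–4% |
| 0.20 | 0.926–0.974 | about 3–7% |

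The gain is thus about 1 to 8% at most. If PHC variance fell by the same share, the ratio at R² = 0.20 would be √0.80 = 0.894, a reduction of about 11%.

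**The case against.** The strongest reply is that this is silence, not error. The quoted clause says how two effects are treated and is not a full list of terms. Nothing in the section forbids adjustment, and a covariate list commonly sits in an analysis plan that is not shown here. That is right, and it is why the point is offered as an improvement. What remains is that the article does set out the model's structure, and the design it describes makes patient adjustment more than routine.

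The safeguards also count. Patients are blind to the allocation scheme, inclusion is deliberately broad, and there are SOPs and uniform volunteer training. A research assistant is on site throughout, and the analyst is blinded. These make selection less likely, but none of them checks or corrects a difference in who agrees to take part.

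Two stronger readings are tempting and are not supported:
- **Chance imbalance biases the effects.** A reader might infer this from small cells of new patients. Step 2 shows that it does not.
- **Unblinded staff select the patients.** The Recruitment section does not say who enrols, and the Blinding section names doctors and researchers, not volunteers. Volunteers delivering patient education plainly know they are doing so, but no passage says that selection will occur.

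Finally, adjustment is not automatically safe for every characteristic. Habit 2 asks patients to identify their main concern for the visit, so a reason for visit reported afterwards could itself be affected by the intervention.

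**Conclusion.** The point holds as a cheap improvement. The stated model offers no protection against a condition-linked change in case mix within a PHC, in a design where patients enter after the condition is set and the staff who deliver the patient intervention also collect the outcomes. Whether such a change will happen cannot be told from the document.

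If it does, the bias is covariate effect times shift: about 0.03 to 0.05 SD for a 10-point shift in a characteristic worth 0.3 to 0.5 SD. Type I error is then about 6 to 9% for one common effect in two assumed layouts, and less in the third layout or for three separate effects. Shift, covariate effect, layout and outcome SD are all assumptions, so the percentages of the 0.13 target are illustrations and not findings about this trial. The precision gain of about 1 to 8% does not need selection to occur, but it does rest on an assumed R² of 5 to 20%.

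**What to change.** In the Statistical analysis section, prespecify a short set of patient-level fixed effects that the intervention cannot change: age, sex, education, first or return visit, and respondent type (patient or accompanying family member). State whose age and education are meant when a family member answers. Ask these items identically in all conditions. Include chronic or acute reason for visit only if it is recorded before the intervention.

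Report the model without these terms as a sensitivity analysis. Tabulate the characteristics by condition and period, so that a shift in case mix can be seen.

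The cost is a sentence or two of analysis text, a few items on a questionnaire already in use, and a few extra parameters, which is small against 1272 patients. Adjustment removes only selection on measured characteristics; the table helps a reader judge how far to worry about the rest.

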**Methods:**

A cross-sectional incomplete stepped-wedge cluster randomized trial design will be conducted in 8 primary healthcare institutions (PHCs). Following phase I of “usual care” as control measures for each PHC, either a patient- or doctor-only intervention will be implemented in phase II. In phase III, both patients and doctors will be involved in the intervention. This study will be conducted simultaneously in Nanling County and West Lake District. The primary outcomes will be evaluated after patients complete their visit: (1) patient literacy, (2) sense of control and (3) quality of doctor-patient communication. Finally, a mixed-effects model and subgroup analysis will be used to evaluate the effectiveness of the interventions.

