#### Intervention 3 (POFHM): FHM both for doctors and patients

The primary focus of the complete POFHM is to cultivate patient visit habits and encourage doctors to provide positive feedback for patients. As we emphasized in the previous section, the construction of the DPR is the result of the joint efforts of both sides. Therefore, the researchers hypothesized that complete POFHM, targeting both doctors and patients, would achieve the best effects.

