### Primary outcomes

This patient-oriented, physician-supported intervention incorporates the sense of control theory in its design. The intervention focuses on improving patient literacy, with the ultimate goal of effectively improving the quality of DPC.

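### Three unordered primary outcomes and three interventions share one unadjusted 5% level, and the sample size spends that full 5% on a single unspecified DPC contrast

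*Protocol article*

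**What the plan says.** The protocol article gives three outcomes primary status. The Abstract lists them as "1) patient literacy, (2) sense of control and (3) quality of doctor-patient communication", and the Primary outcomes section describes an instrument for each. No order is set, although that section describes the intervention as working "with the ultimate goal of effectively improving the quality of DPC".

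The Statistical analysis section applies the analysis to every outcome and every intervention: "For all primary outcomes, an intention-to-treat analysis will be performed", and "To evaluate the effects of the primary outcomes of the three interventions, generalized linear mixed models will be used". It closes with one error rate: "A 2-tailed error rate of 5% will be used to test the hypothesis".

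The description of Intervention 3 gives the one expectation worded as a hypothesis: "the researchers hypothesized that complete POFHM, targeting both doctors and patients, would achieve the best effects". The Discussion adds that the design serves to compare involving one party with involving both.

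The Sample size section rests on DPC alone ("an absolute increase of 0.13 or more in DPC scores for patients is meaningful"). It claims 80% power at two-sided 5% with 1272 patients, raised to 1590 for missing data. It does not say to which of the three interventions the 0.13 applies.

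**The concern.** The error rate is given for one hypothesis, but the primary analysis covers nine intervention-versus-control comparisons. The hypothesis that the combined intervention (I-B) does best adds two more contrasts per outcome, against patient-only (I-P) and doctor-only (I-D). The analysis section describes no test of these.

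Two things are at stake. First, the text does not fix which result would make the trial positive, so its false-positive rate depends on a rule that could be chosen after the data are seen. Second, the protocol has already committed the full 5% in the sample size. An adjustment added later across the stated family would cut the planned power, and leaving it out inflates the error. The choice of three co-ranked primaries and the choice of sample size therefore pull against each other.

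**Working it through.** **The plan's own figures.** 1272 / 53 per site and interval = 24 site-intervals, or 3 for each of 8 sites: 8 × 3 × 53 = 1272. Allowing 20% missing, 1272 / 0.80 = 1590. Both counts reproduce. The 80% power cannot be checked, because no standard deviation is given and the design figure is not shown. The protocol states no family-wise error rate to reproduce.

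**Inputs.** Three outcomes and three interventions (Abstract; Statistical analysis), so 3 × 3 = 9 tests against control, each at two-sided 5%, or 2.5% in the direction of benefit. The condition examined is that no intervention affects any outcome and that any one significant result counts as success. The second part is an assumption.

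**Independent tests.**
- At least one significant result in either direction: 1 − 0.95^9 = 0.370.
- At least one false claim of benefit: 1 − 0.975^9 = 0.204.
- One intervention over three outcomes: 1 − 0.95^3 = 0.143 in either direction; 1 − 0.975^3 = 0.073 for benefit.

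**Correlated tests.** The three interventions share control data and the three outcomes come from the same patients, so the tests are correlated. The protocol gives no correlations, and those below are assumptions. Nine normal test statistics were simulated (1,000,000 draws), with the correlation between two tests taken as outcome correlation × intervention correlation. The staircase row uses intervention correlations 0.49, 0.65 and 0.65. They come from a mixed model on an assumed layout with the protocol's intra-cluster correlation of 0.034 and 53 patients per site-interval.

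| Intervention correlation | Outcome correlation | Any significant | Any false benefit |
|---|---|---|---|
| 0.5 | 0 | 33.1% | 17.7% |
| 0.5 | 0.5 | 29.4% | 14.9% |
| 0.5 | 0.7 | 25.9% | 13.0% |
| 0.7 | 0 | 29.2% | 15.5% |
| 0.7 | 0.7 | 22.7% | 11.3% |
| assumed staircase | 0 | 31.3% | 16.6% |
| assumed staircase | 0.7 | 24.3% | 12.2% |

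The range is therefore about 23–33% for any significant result and 11–18% for a false benefit. It has no fixed floor: at outcome correlation 0.9 with interventions at 0.5–0.7, the chance of any significant result is 18–20%.

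**The opposite success rule.** If some intervention had to succeed on all three outcomes, the chance was at most 2.4% in the cases run.

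**What a later adjustment would do to power.** Take the stated 80% at face value (normal approximation). The standardised effect is 1.960 + 0.842 = 2.802.
- At 0.05/3 = 0.0167 the critical value is 2.394, and power is Φ(2.802 − 2.394) = Φ(0.408) ≈ 66%.
- At 0.05/9 = 0.0056 it is 2.773, and power is Φ(0.029) ≈ 51%.

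**The case against.** The strongest reply is that testing order, multiplicity and success criteria usually belong to the statistical analysis plan, which is not shown, and that a journal article condenses. That stands as far as it goes: the lack of a named adjustment method is not the point here. It does not remove the point, because the document itself fixes three co-ranked primaries, evaluates all three interventions on each, states one level, and sizes the trial at that full level for one contrast. A later plan cannot adjust across that family without undercutting the stated power.

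Three stronger readings are tempting, and the documents support none of them:
- A reader might take the 37%, or the correlated figures near it, as the chance of wrongly declaring an intervention effective. Those figures count significance in either direction, including apparent harm. The figure for false benefit is about half as large.
- A reader might infer that the protocol lets any one of nine results count as success. It gives no success rule either way. The wording on a single hypothesis, the goal of better DPC and the DPC-only sample size could equally point to a narrower test.
- A reader might infer that superiority of the combined intervention will be claimed by setting p-values against control side by side. The Discussion states an intention to compare single-party with both-party intervention. What is missing is a matching contrast in the analysis section, not the intention.

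**Conclusion.** The point holds in this form. The protocol ties nine primary comparisons to one unadjusted two-sided 5% level without saying which is confirmatory, and it sizes the trial for one DPC difference without naming the intervention. The error figures in the working are conditional: they apply if any single significant result counts, under no effect anywhere, and the correlated values rest on correlations and a layout that the protocol does not give. Under a rule requiring all three outcomes they would not apply. That the error rate can run from under 5% to over a third, depending on an unstated rule, is the reason to settle the rule now.

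**What to change.** 1. In the Statistical analysis and Sample size sections, name DPC (CARE), I-B versus control, as the single confirmatory test at two-sided 5%. State that the 0.13 difference refers to this contrast. This follows the protocol's own priorities: DPC is the goal and the only outcome sized, and I-B is the lead hypothesis.
2. Put all other confirmatory tests into one pre-specified procedure, opened only if the first test succeeds: either one fixed sequence or one Holm family at 5% overall. Include sense of control and patient literacy for I-B versus control, and I-P and I-D versus control on DPC. Do not open two branches at 5% each, because with independent tests that allows 1 − 0.95^2 = 9.75%.
3. Base any claim that I-B is best on direct I-B versus I-P and I-B versus I-D contrasts, both significant. Do not make these a gate for I-P versus control, since the Background gives educating patients priority.

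Cost: mainly wording, settled before the outcome data are analysed. The first test keeps the full 5%, so multiplicity alone adds no patients, provided the existing calculation was made for I-B versus control. If it was made for another contrast, it must be redone. The protocol shows no power for the head-to-head contrasts, so a claim of superiority over the single interventions may be out of reach. The downside is that a significant result on patient literacy or sense of control alone would no longer count as trial success.
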